## Abstract

**Background:**

Zinc deficiency poses significant health risks, particularly in low-income settings. This study aims to evaluate the impact of agronomically zinc biofortified (fermented and non-fermented) and post-harvest wheat flour flatbread on zinc status and metabolic health in adolescents and adult women in rural Pakistan.

**Methods:**

A four-arm triple-blind randomized controlled trial will be conducted in a rural district of Pakistan. Participants (adolescents aged 10–19 and adult women aged 20–40) will be assigned to receive fermented or unfermented high zinc agronomically biofortified wheat flour flatbread, post-harvest zinc-fortified wheat flour flatbread, or low zinc conventional whole wheat flour flatbread. The meal would be served once a day, six days a week for six months. The study aims to enroll 1000 participants and will be analyzed based on the intention-to-treat principle. The trial is registered with number NCT06092515.

**Outcomes:**

Primary outcomes will include serum zinc concentration and metabolic markers, while secondary outcomes include anthropometric measurements, blood pressure, and dietary intake.

**Conclusion:**

This trial will provide valuable insights into the efficacy of agronomically zinc biofortified wheat flour in improving zinc status and metabolic health. Findings may inform public health strategies to combat zinc deficiency in resource-limited settings.

## Introduction

Zinc is integral to numerous essential metabolic pathways and usually manifests as a rather nonspecific deficiency, with varying severity and varies by age [1]. In childhood, zinc deficiency appears as growth retardation and cognitive impairment [2, 3], recurrent infections including diarrhea [4], loss of hair, conjunctival and eyelid inflammation. In adolescents and adults, zinc deficiency can lead to fertility issues, reduced work capacity and metabolic disorders [5, 6] whereas for the elderly population, recurrent infections are a common manifestation [7].

Zinc supplementation, administered in pharmacological doses via pills or syrups, has demonstrated several positive effects in different age groups. In children, zinc supplementation suggests improvement in mean serum zinc concentration [8, 9] and reduction in the incidence of diarrhea and its morbidity but has shown no effect on pneumonia and malaria morbidity [10–12] and evidence also suggests a small improvement in height [8, 9]. There is no convincing evidence for the effectiveness of zinc supplementation on pregnant women except for a small effect on preterm births in low- and middle-income countries [13]. In adults with insulin resistance, zinc supplementation does not appear to prevent the onset of type 2 diabetes [14], while zinc supplementation for individuals aged 55–87 has shown to reduce the incidence of infections and improve plasma zinc concentration [15]. The potential impact of zinc on atherosclerotic disease remains inconclusive, despite its theoretical benefits in reducing plasma lipid peroxidation end products and endothelial cell adhesion molecules [16]. A recent meta-analysis suggests that low-dose, long-term zinc intake from supplements, and potentially biofortification, may offer benefits in terms of risk factors for type 2 diabetes (T2DM) and cardiovascular disease (CVD) [17].

Zinc bioavailability from a mixed or vegetarian diet based on refined cereal grains is estimated to be 26–34%, whereas 18–26% is absorbed from an unrefined cereal-based diet [18]. The actual amount of absorbed zinc not only depends on the zinc content of the consumed diet but is highly affected by its intestinal zinc bio-accessibility and bio-availability [18]. The inhibitory effect of phytate on zinc absorption is concentration-dependent and has shown to be more important than the phytate content of the product itself [19]. Fermentation theoretically results in higher zinc bioavailability if a significant reduction of phytate is achieved.

Food fortification with zinc appears as an attractive public health strategy, with numerous programs initiated in developing countries as a cost-effective way to combat zinc deficiency [1, 12]. Systematic reviews evaluating zinc fortification indicate significant improvements in plasma zinc concentration, reduced prevalence of zinc deficiency, increased child weight, and enhanced short-term auditory memory. However, data for adolescents, pregnant women, and lactating women are limited [20]. Biofortified zinc flour have also shown mixed effects [21].

The aim of this randomized controlled trial (RCT) is to assess the effect of fermented and unfermented wheat flour flatbread from agronomically zinc biofortified and post-harvest fortified wheat flour when compared to conventional low-zinc wheat flour flatbread and its impact on health including zinc status, anthropometric outcomes, risk of T2DM and morbidity on adolescent and adult females. In Pakistan, common naan is a type of flatbread, is typically made from fermented maida (all-purpose low extraction) wheat flour, characterized by refined flour with minimal bran and germ. However, in most households, the community usually uses unfermented whole wheat flour flatbread. Wheat samples from various sites across Pakistan were tested, with zinc levels ranging from 20-50mg/kg. The trial chose two wheat varieties: conventional low zinc (20-25mg/kg) and high zinc content which is agronomically biofortified (>35mg/kg) which was grown under collaborator supervision at the study site.

## Materials and methods

### Objectives

The objective of this trial is to assess the effect of whole wheat flatbread made from agronomically biofortified ’high zinc wheat’—(fermented and unfermented) and ’post-harvest zinc-fortified wheat flour’ compared to conventional ’low zinc’ whole wheat flatbread on zinc status and metabolic health in adolescents (10–19 years) and adult women (20–40 years).

### Study design

This would be a four arm individually randomized, triple-blind trial conducted in a rural district of Pakistan. The study will adhere to the guidelines outlined in the Consolidated Standards of Reporting Trials (CONSORT) for RCTs [22]. The trial is registered at clinicaltrials.gov with number NCT06092515 [23]. Fig 1 highlights the SPIRIT schedule of the trial (S1 Checklist).

**Fig 1 pone.0304462.g001:**
[figure not shown]
SPIRIT schedule of EZAFFAW trial.

### Intervention

Participants will be randomly divided into four groups according to the four-arm design in a 1:1:1:1 ratio (See **Fig 2** for study groups).

**Fig 2 pone.0304462.g002:**
[figure not shown]
Study groups.

Group 1: will receive fermented high zinc agronomically biofortified wheat (>35mg/kg) flour flatbread.Group 2: will receive unfermented high zinc agronomically biofortified wheat (>35mg/kg) flour flatbread.Group 3: will receive fortified (post-harvest) whole wheat (80mg/kg) flour flatbread.Group 4: will receive low zinc conventional whole (20–25 mg/kg) wheat flour flatbread.

The intervention duration will be six months, and participants will be provided with the respective ‘flatbread’ with a vegetable curry or pulse (*daal*) meal once a day for six days a week for six months This meal would be distributed at schools/colleges or community spaces during break or after the school is over.

### Outcomes

#### Primary

Serum zinc concentrationZinc deficiencyHbA1CHOMA-IR (cut-off >2) [24]Lipid profile (total cholesterol, very low-density lipoprotein (VLDL), low-density lipoprotein (LDL), high-density lipoprotein (HDL); triglycerides (TGs))

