### Sample size and sampling strategy

#### Sample size calculation

The study sample size was calculated based on an individually randomized four arm design on the primary outcomes of mean serum zinc levels and HbA1c. The mean HbA1c taken was 5.62% (SD 1.96) [33] and mean serum zinc was 79.5 μg/dL (SD 35.9) according to NNS-2018 [1]. The sample size was determined with a power of 0.8 and alpha of 0.05 to detect a difference of at least 0.12 effect size in the mean serum zinc levels between groups and to detect a 0.2 effect size in the mean HbA1c levels with a dropout rate of 10%. The sample size calculated was 250 participants in each group, with 210 adolescents (aged 10–18 years) and 40 adult women (aged 20–40 years). Hence, a total of 1000 participants would be randomly allocated to each of the groups in a 1:1:1:1 ratio.

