### Trial analysis

This trial will adhere to CONSORT guidelines for randomized trials, with primary analysis on an intention-to-treat basis [22]. Both primary and secondary data will be analyzed following the same principle. Descriptive statistics will include mean and standard deviation for symmetrically distributed continuous variables, median and interquartile range for asymmetrically distributed ones, and frequency with percentages for categorical data. Associations between dependent and independent categorical variables will be accessed using chi-square test, while one-ANOVA will be used to assess difference in continuous outcomes by intervention groups. Significant association further assessed by post-hoc test adjusting for multiple comparisons. Multivariate analysis will be performed using mixed effect linear or logistic regression to assess the impact of intervention over time by including time and group interaction. The time and intervention group will be treated as fixed effect while students included in the model as random intercept. The potential confounding factors that are imbalance at baseline will also be included as fixed effect in the model. The minimal adequate model for regression will be computed using the backward procedure. Statistical Significance will be set at p-value of <0.05. To assess the robustness of the findings, a sensitivity analysis will be conducted, and a dose-response relation will also be assessed.

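### Nine unranked primary outcomes are judged at one 0.05 threshold, with adjustment stated only for post-hoc comparisons, so the chance of some false-positive primary result is well above 5%

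*Protocol article*

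**What the plan says.** The list under Outcomes, Primary, begins "Serum zinc concentrationZinc deficiencyHbA1CHOMA-IR (cut-off >2) [24]Lipid profile" and breaks the lipid profile into "total cholesterol, very low-density lipoprotein (VLDL), low-density lipoprotein (LDL), high-density lipoprotein (HDL); triglycerides (TGs". Written out, this is serum zinc, zinc deficiency, HbA1c, HOMA-IR and five lipid fractions. No item is placed above another, and there is no composite and no testing order.

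The sample size section uses only two of these. The calculation is based "on the primary outcomes of mean serum zinc levels and HbA1c" and was done "with a power of 0.8 and alpha of 0.05". Alpha is not divided between the two.

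The Trial analysis section gives three relevant rules:

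- An ANOVA "will be used to assess difference in continuous outcomes by intervention groups", with chi-square tests for categorical outcomes, followed by: "Significant association further assessed by post-hoc test adjusting for multiple comparisons".
- A mixed model to "assess the impact of intervention over time by including time and group interaction", with no adjustment mentioned.
- One threshold for everything: "Statistical Significance will be set at p-value of <0.05".

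**The concern.** In context, the only stated adjustment applies to comparisons between arms once a given outcome has shown a group difference. It does not limit how many outcomes get a first-stage test at 0.05. As written, all nine measures stand as primary, each with its own full 0.05.

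The two parts of the protocol also imply different primary sets: two outcomes for sizing and nine for inference. Seven of the nine (HbA1c, HOMA-IR and the five lipid fractions) bear on metabolic health, which the objective names alongside zinc status. A chance result on one of them could be reported as a primary metabolic finding, and nothing in the text says how a reader should discount it.

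**Working it through.** **Inputs from the protocol.** Nine primary measures, or five with the lipid profile as one item; threshold 0.05; two sizing outcomes; power 0.8; 10% dropout; 250 per arm in four arms; serum zinc mean 79.5 and SD 35.9; effect sizes 0.12 (zinc) and 0.2 (HbA1c), with the type of effect size not stated. Tests are taken as two-sided, which is an assumption. The protocol gives no family-wise error rate and no correlations between outcomes.

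**The plan's own figure, 250 per arm.**
- If 0.12 is a 12% relative difference: 0.12 × 79.5 = 9.54, and 9.54/35.9 = 0.266 SD. A two-group comparison at alpha 0.05 and power 0.8 needs 223 per arm, and 223/0.9 gives 248. This is close to 250.
- If 0.12 is Cohen's f in a four-group ANOVA: 191 per arm, or 213 after dropout. This does not give 250.
- If 0.12 is Cohen's d: 1091 per arm, or 1213 after dropout. This is far off.

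The first reading fits best, but the protocol does not confirm it, so the first two are both carried forward.

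**Family-wise error, no true effect on any outcome, any single primary claimable.** For k independent tests the chance of at least one false positive is 1 − 0.95^k.

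| Set of outcomes | Calculation | Result |
|---|---|---|
| Nine measures | 1 − 0.95^9 = 1 − 0.630 | 37.0% |
| Five items (lipid profile as one) | 1 − 0.95^5 = 1 − 0.774 | 22.6% |
| Two sizing outcomes | 1 − 0.95^2 = 1 − 0.9025 | 9.75% |

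The outcomes are in fact correlated; zinc deficiency, for example, is derived from serum zinc. Simulating nine equally correlated omnibus tests with 3 degrees of freedom (200,000 draws) gives:

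| Assumed common correlation | At least one false positive |
|---|---|
| 0.3 | 33% |
| 0.5 | 28% |
| 0.7 | 21% |
| 0.8 | 17% |
| 0.9 | 13% |

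Simulating single two-sided contrasts instead gives figures within about one percentage point. An assumed block structure (a zinc pair, a glycaemic pair and a lipid block) gives 31%. The limit at perfect correlation is 5%.

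**Power if alpha is controlled.** Evaluable participants: 250 × 0.9 = 225 per arm, 900 in total.

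| Reading of 0.12 for serum zinc | Alpha 0.05 | Alpha 0.025 (Holm, first step) |
|---|---|---|
| Cohen's f, four-arm ANOVA | 86.8% | 79.9% |
| 12% relative difference, two arms | 80.3% | 71.5% |

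Under Holm, serum zinc is tested at 0.05 once HbA1c is significant at 0.025, so the first column then applies. For comparison, Bonferroni over all nine (0.05/9 = 0.0056) would take ANOVA power at f = 0.12 from 87% to 63%.

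**The case against.** The strongest reply is that an ordering of endpoints or a correction across them commonly belongs in the statistical analysis plan, which is not shown. The article is silent on the matter; it does not rule a correction out. That stands, and it limits the point to what the protocol itself fixes: an unranked list of nine, one threshold, and a sample size built on two.

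A reader might infer that the trial has no error control. The text does not support that. Each outcome has an omnibus test at 0.05 and then adjusted comparisons, so error within a single outcome is addressed on that route.

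A reader might also take 21% to 37% as the established error rate. It is not. The lower end needs an assumed correlation of 0.7 and is not a floor. All these figures also assume that one positive primary is enough for a claim; the protocol neither states that rule nor excludes it.

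It would also be too strong to say that Holm costs nothing. That holds only against the nominal 80%, and only if 0.12 is Cohen's f, a reading that does not reproduce 250 per arm.

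Finally, the cut-off printed beside HOMA-IR might be read as a commitment to a binary analysis that wastes data. The list does not say so, and the analysis section provides methods for both continuous and categorical outcomes.

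The choice of primary outcomes is partly the sponsor's, and changing their status after enrolment has begun is more than a wording edit. Both points bear on the remedy and do not remove the defect.

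**Conclusion.** The point holds in a limited form. Followed as written, the protocol tests nine unranked primaries at 0.05 each, and the only adjustment it states does not act across outcomes. The resulting chance of at least one false-positive primary is 37% at independence. It stays above twice the nominal 5% even at an assumed common correlation of 0.9. Counting the lipid profile once softens this but does not cure it.

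The conclusion rests on four assumptions: no true effect on any outcome, freedom to claim any one primary, the correlations shown, and no hierarchy in an analysis plan outside the article. It is a matter to settle before unblinding and does not call the trial's design into question.

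**What to change.** Before unblinding, and subject to anything an existing analysis plan already fixes:

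1. Name serum zinc and HbA1c as the confirmatory primary outcomes, tested with Holm at overall 0.05.
2. Report zinc deficiency, HOMA-IR and the five lipid fractions as supportive, with confidence intervals. If the sponsor wants to keep them primary, test them in a stated fixed order after the first two.
3. State that HOMA-IR is analysed as a continuous measure, with the proportion above 2 as a supporting summary.
4. Say what kind of effect size 0.12 is, so that the power cost can be read off.

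No new data or participants are needed. The costs are that the supportive outcomes lose stand-alone confirmatory status, that the registry needs a dated update because enrolment began in August 2023, and that serum zinc loses power whenever it must pass at 0.025. That loss is about 7 points if 0.12 is Cohen's f (86.8% − 79.9%) and about 9 points if it is a 12% relative difference (80.3% − 71.5%). It is recovered once HbA1c is significant.

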#### Secondary

Body Mass Index (BMI)—Severe thinness, thinness, normal weight, overweight, obeseRed blood cell membrane fatty acids concentrationsAnemiaBlood PressureSchool attendanceMorbidity–Diarrhea, Acute respiratory infection (ARI) etc.

#### Compliance

Number of days each participant had flatbread.Flatbread consumed (weight) each day.

### Eligibility criteria

The study will include adolescents (aged 10–19 both male and female) and adult women (aged 20–40). Participants would be eligible if they can consume wheat flour (no celiac disease), are not severely malnourished, pregnant, or lactating at enrollment, with no known chronic disease, and not enrolled in any other nutrition program or taking micronutrient supplements. Individuals planning to leave the study site during the study period will also not be eligible. The enrollment has started in Aug 2023.

For the adult women, an additional eligibility criterion will be to assess their risk for T2DM. These risk factors were modified from an existing risk assessment scale, FINDRISC (Finnish Diabetes Risk Score) and Type 2 Diabetes Risk Test by American Diabetes Association (ADA) [25, 26]. Adult women with any one of the following risk factors will be eligible to be enrolled in the study.

BMI (>25kg/m^2^)Waist circumference (> 31 inches)Family history of diabetesHbA1c (>5.1%)FBG (>100mg/dl)Homeostatic Model Assessment of Insulin Resistance (HOMA-IR) (>2)

The HbA1c threshold for prediabetes are lower in Pakistan population compared with international guidelines, hence we have kept this as 5.1% [27].

### Study site

The study will be conducted in Mithi located in district Tharparkar in the province of Sindh, Pakistan. Tharparkar is an impoverished district of Sindh, characterized by a tropical desert climate and is located about 320 kms east from the provincial capital Karachi [28], and has a total area of 19,637 km^2^ and a population of 1,647,036 (rural: 1,514,502; urban: 132,534) of which 53.4% are males and 46.4% are females [29]. A staggering 87% of its population lives below the poverty line [30], due to limited economic opportunities and dependence on seasonal rains [31]. Administratively, it is divided in seven talukas and subdivided in 44 union councils [28]. The district experiences erratic annual rainfall, sometimes as low as 100mm, leading to droughts [32]. In Sindh about 58.8% of the adolescent girls are anemic of which 63.1% are from rural districts of Sindh, while 21.4% women aged 15–49 years old have zinc deficiency [1]. Tharparkar has high food insecurity [1], with 60% of the children under five stunted, 33.3% wasted, 19.8% with both stunting and wasting and 40.4% of the non-pregnant women of reproductive age are underweight [1]. The population of Mithi are predominantly vegetarians.

We have selected two high schools in Mithi where we would enroll adolescents and an elementary college, midwifery college and the neighboring community for adults 20–40 years of age. A list of current students from the respective school/colleges and individuals residing in the community (not attending school) will be collected through household line listing. All individuals on this list will undergo an eligibility assessment and will be individually randomized to the four groups.

We will obtain written informed consent from all eligible participants, and assent from participants under 18 years of age and consent from their caretakers. Upon receiving consent, the list of eligible adolescents and female adults will be randomly assigned to one of four groups, which would be blinded, and color coded as red, blue, green, and black.

### Sample size and sampling strategy

#### Sample size calculation

The study sample size was calculated based on an individually randomized four arm design on the primary outcomes of mean serum zinc levels and HbA1c. The mean HbA1c taken was 5.62% (SD 1.96) [33] and mean serum zinc was 79.5 μg/dL (SD 35.9) according to NNS-2018 [1]. The sample size was determined with a power of 0.8 and alpha of 0.05 to detect a difference of at least 0.12 effect size in the mean serum zinc levels between groups and to detect a 0.2 effect size in the mean HbA1c levels with a dropout rate of 10%. The sample size calculated was 250 participants in each group, with 210 adolescents (aged 10–18 years) and 40 adult women (aged 20–40 years). Hence, a total of 1000 participants would be randomly allocated to each of the groups in a 1:1:1:1 ratio.

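### The 80% power claim rests on an undefined 'effect size': in the usual standardised sense it is not met, and on the reading that gives 250 per arm it covers only one unadjusted zinc comparison

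*Protocol article*

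**What the plan says.** All inputs are in the Protocol article, section Sample size calculation.

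- Error rates: "The sample size was determined with a power of 0.8 and alpha of 0.05". Sidedness is not given.
- Zinc target: "to detect a difference of at least 0.12 effect size in the mean serum zinc levels between groups".
- HbA1c target: "to detect a 0.2 effect size in the mean HbA1c levels with a dropout rate of 10"%.
- Planning values: "mean serum zinc was 79.5 μg/dL (SD 35.9) according to NNS-2018", and for HbA1c a mean of 5.62% with SD 1.96.
- Result: "The sample size calculated was 250 participants in each group, with 210 adolescents" and 40 adult women, 1000 in total over four equal arms.

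The Objectives section sets three intervention breads "compared to conventional ’low zinc’ whole wheat flatbread on zinc status and metabolic health", which makes three contrasts with control. The Discussion also presents the trial as comparing biofortified with post-harvest fortified wheat directly, and as examining fermentation, so contrasts between intervention arms matter too. The Trial analysis section plans a one-way ANOVA for continuous outcomes, followed by post-hoc tests corrected for multiplicity.

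**The concern.** A difference between group means given as an 'effect size' is ordinarily read in SD units. On that reading the trial claims to detect 0.12 × 35.9 = 4.3 μg/dL of zinc and 0.2 × 1.96 = 0.39 HbA1c points. It cannot do so with 250 per arm.

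Other meanings of the same words give very different differences and sample sizes, and the section does not say which applies. What is at stake is interpretation. A reader who takes the usual meaning would treat a null zinc result as excluding effects less than half the size that the trial can detect. In addition, the quoted power takes no account of the several adjusted comparisons on which the conclusions will rest.

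**Working it through.** **Inputs.** From Sample size calculation: alpha 0.05, power 0.80, dropout 10%, zinc mean 79.5 and SD 35.9, HbA1c mean 5.62 and SD 1.96. Evaluable per arm: 250 × 0.9 = 225. Two-sided testing is my assumption. I use the normal approximation; the exact t-test changes power by a few tenths of a percentage point and n by about one.

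Formulas:
- n per arm = 2(z₁₋α/₂ + z₁₋β)² / d² = 2(1.960 + 0.842)² / d² = 15.70 / d²
- enrolled = n / 0.9
- power at 225 = Φ(d√(225/2) − z₁₋α/₂) = Φ(10.607d − 1.960)

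**1. Reproducing 250 per arm: 0.12 and 0.2 as fractions of the means.**
- Zinc: 0.12 × 79.5 = 9.54 μg/dL; d = 9.54/35.9 = 0.266; n = 223; 223/0.9 gives 248 enrolled. Power at 225 = Φ(2.819 − 1.960) = 80.5% (80.3% by t-test).
- HbA1c: 0.2 × 5.62 = 1.124 points; d = 1.124/1.96 = 0.573; n = 48; 54 enrolled. Power at 225 exceeds 99.9%.

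The larger requirement, 248, is the stated 250 to within rounding.

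**2. The usual meaning: standardised mean difference between two arms.**
- Zinc, d = 0.12: n = 1,091; 1,213 enrolled. Power at 225 = Φ(1.273 − 1.960) = 25%.
- HbA1c, d = 0.2: n = 393; 437 enrolled. Power at 225 = Φ(2.121 − 1.960) = 56%.

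One-sided testing does not rescue this reading (35% and 68%).

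**3. Cohen's f in a four-group ANOVA (noncentral F, alpha 0.05).**
- f = 0.12: 191 per arm, 213 enrolled; power at 225 is 87%.
- f = 0.2: 70 per arm, 78 enrolled; power exceeds 99%.

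Both exceed 80%, but the calculation returns 213 rather than 250. Halving alpha to 0.025 for two outcomes gives 252 for zinc, but the section mentions no such split.

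**4. Effect of multiplicity on the reproducing reading (zinc, d = 0.266, 225 per arm).** The correction method is not named; Bonferroni is assumed.

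| Comparisons | Critical z | Power |
|---|---|---|
| 1 | 1.960 | 80% |
| 3 (each bread against control) | 2.394 | Φ(2.819 − 2.394) = 66% |
| 6 (all pairs) | 2.638 | Φ(2.819 − 2.638) = 57% |

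HbA1c at 1.12 points stays above 99% throughout.

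**5. Difference from control detectable at 80% power with 225 per arm**, whatever the authors meant:
- Unadjusted: (1.960 + 0.842)/10.607 = 0.264 SD, or 9.5 μg/dL zinc and 0.52 HbA1c points.
- Three comparisons: (2.394 + 0.842)/10.607 = 0.305 SD, or 11.0 μg/dL and 0.60 points.

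**The case against.** The strongest reply is that the calculation is sound and only loosely worded. The section quotes means as well as SDs; a standardised effect would not need the means, while a relative difference does. That reading uses only the section's own figures and lands on 248. This stands. A reader might infer that no reading yields 250 per arm with 80% power for both outcomes, or that the trial is underpowered at 25% and 56%. The documents support neither: the relative reading reproduces 250, and Cohen's f also exceeds 80% for both outcomes.

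A reader might also conclude that 0.12 and 0.2 must be Cohen's f, because ANOVA is planned. The section does not say so, and f fits the stated number less well than the relative reading does. Nor does it say that HbA1c power rests on the 40 women per arm. The calculation is for 250 per group, and HbA1c is measured in participants generally, so power figures for the women alone would answer a claim that the protocol does not make.

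On multiplicity, a less conservative method than Bonferroni would lose less power. Baseline adjustment could also recover it: 80% over three contrasts needs 297 per arm without a covariate, so a baseline-endline correlation of about √(1 − 225/297) = 0.49 would suffice under ANCOVA. That is fair, but the section states no correlation and claims no such gain.

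What the reply does not remove is that the relative reading is inferred, and that even on it the 80% belongs to one unadjusted comparison.

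**Conclusion.** The point holds as a defect in how the target and power are stated, not as a finding that 1000 participants are too few. Depending on what 'effect size' means, the zinc target requires 1,213, 248 or 213 enrolled per arm. In the usual standardised sense the claimed 80% is really 25% for zinc and 56% for HbA1c. On the reading that reproduces 250, the zinc target is 9.5 μg/dL and the 80% is correct for one unadjusted two-arm test, but falls to about 66% for the three contrasts with control and 57% for all six pairs. HbA1c is not affected on that reading.

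These figures assume two-sided tests, 10% dropout spread evenly over the arms, the quoted SDs, no gain from baseline adjustment and, for the adjusted figures, Bonferroni. The paragraph should be corrected because the interpretation of null results depends on it.

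**What to change.** Keep 1000 participants and rewrite the one paragraph:

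- Replace 'effect size' with the target actually used, as an absolute difference. If it was 12% and 20% of the mean, that is 9.5 μg/dL zinc and 1.12 HbA1c points. Name the test and its sidedness.
- State the difference from control detectable at 80% power with 225 evaluable per arm: 9.5 μg/dL zinc and 0.52 HbA1c points unadjusted; 11.0 μg/dL and 0.60 points with Bonferroni over three comparisons.
- Either limit the 80% claim for zinc to a single unadjusted comparison, or give the power under the planned adjustment.
- Do not describe 0.12 and 0.2 as Cohen's f unless that was the calculation. If it was, say so and report the power for the four-group test separately from the pairwise figures.

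The cost is wording only, with no further recruitment. The downside is that the stated sensitivity becomes slightly less favourable.
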